#### Tripartite Network Analysis

The tripartite network analysis will be used to integrate information from the fecal microRNA characteristics, specific gut microbiota, and clinical data for constipated patients in the VA and SA groups. The interaction among the clinical efficacy (amelioration of SCC symptoms), microRNA characteristics (the differential expression of miRNAs in the stool), and fecal microbiome (stool microbial community) will be investigated by computing Spearman's correlations in Matlab (version R2015b). An effect size of *r* = 0.10 is considered less (1% variance explained), 0.30 moderate (9% variance explained), and 0.50 large (25% variance explained). Fisher's *r*-to-*z* transformation will be adopted to investigate the correlation coefficient difference between groups (acupuncture-sham acupuncture), using the *Z*-test. Significance will be considered at uncorrected *p* < 0.05. The Cytoscape (version 3.8.2) will be used to generate and visualize the phenome, fecal microbiome, and differentially expressed miRNAs interaction network. The networks will be presented based on selecting the gut microbiota counts and their first neighbors as nodes and all adjacent edges. The results will be shown in the line with direct (correlations with fecal microbiome) and indirect effects (clinical symptoms and differentially expressed miRNAs) with an emphasis on the association between microbiome and clinical efficacy. The comparisons between groups will be analyzed using one-way analysis of variance and independent sample *t-*test.

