Electroacupuncture can improve gastrointestinal peristalsis, promote the contraction of distal colon, and accelerate the whole intestinal transport in both healthy and constipated conditions (4). Acupuncture can not only regenerate damaged intestinal neurons and regulate the activities of intestinal nervous system, but also makes effects on serum motilin, ghrelin, gastrin, and bile acid (11). Based on our previous research, intestinal microbiota was identified to play an important role in the improvement of intestinal motility by acupuncture therapy in SCC patients (21). Therefore, the objective of this study is to preliminarily reveal the effector mechanism by which acupuncture regulates miRNAs and gut microbiota.

There are also certain limitations should be noted. First, it is remarkably hard to differentiate IBS-C from SCC using the ROME IV criteria, which makes the differential diagnosis more difficult. Second, the relatively small number of samples and the inability to strictly control the daily diets of participants, which may impact the findings. Third, owing to the short follow-up period, the potential value of miRNAs and gut microbiota in the long-term efficacy of acupuncture will remain unknown. In conclusion, the results of this trial are expected to not only provide clinical evidence of the efficacy of acupuncture in treating SCC, but demonstrate that this efficacy is achieved by modulating the crosstalk between fecal miRNAs and gut microbiota.

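### The tripartite network is tested at an explicitly uncorrected p < 0.05 over an unspecified, probably large number of pairs, which cannot support the Discussion's expected demonstration of mechanism

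*Protocol article*

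**What the plan says.** The Tripartite Network Analysis section of the protocol article combines three layers: symptom improvement, fecal miRNAs and the stool microbiome. Pairs are related by Spearman correlation. For the arms, "Fisher's *r*-to-*z* transformation will be adopted to investigate the correlation coefficient difference between groups (acupuncture-sham acupuncture), using the *Z*-test". The next sentence gives the only significance rule: "Significance will be considered at uncorrected" p < 0.05. The section labels r = 0.10, 0.30 and 0.50 as small, moderate and large. The network is then built by "selecting the gut microbiota counts and their first neighbors as nodes and all adjacent edges". No cut-off on |r|, false-discovery control or permutation check is named.

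The section gives no feature counts. The inputs come from operational taxonomic units at 97% identity (Gut Microbiota Analysis) and from high-throughput sequencing (MicroRNAs High-Throughput Sequencing Analysis), narrowed to selected taxa and differential miRNAs.

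The last sentence of the Discussion expects the results to "demonstrate that this efficacy is achieved by modulating the crosstalk between fecal miRNAs and gut microbiota". The Abstract's Background speaks only of exploring a hypothesis of association, and the end of the Introduction speaks of initial support. The limitations in the Discussion mention the small sample but not multiplicity.

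**The concern.** Declining correction is a stated choice here, not a detail left to an unseen analysis plan. It applies to the analysis that serves the third objective, on how symptom improvement, miRNAs and microbiota interact, and the sample size is itself justified by miRNA and microbiota studies. Correlating three layers of features multiplies the tests quickly. A per-test error rate of 5% then guarantees a stock of chance findings that grows with the number of features kept. If the network is reported as the mechanism of acupuncture, readers cannot tell which edges to believe, and a causal statement would rest on concurrent correlations screened at that level.

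**Working it through.** **The plan's own figures.** The variance labels reproduce: 0.10² = 1%, 0.30² = 9%, 0.50² = 25%. The sample size is 40 per arm; with the stated 20% drop-out, 40 × 0.8 = 32 remain. The article states no number of network tests and no error rate for them, so there is nothing further to reproduce.

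**Expected chance results.** With M miRNAs, T taxa and C clinical measures, the pairs across layers are m = MT + MC + TC. If nothing is related, 0.05 × m results are expected. All counts below are assumptions; C = 5 equals the number of listed outcomes (one primary, four secondary).

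| M | T | C | m | 0.05 × m |
|---|---|---|---|---|
| 3 | 10 | 5 | 30 + 15 + 50 = 95 | about 5 |
| 5 | 20 | 5 | 100 + 25 + 100 = 225 | about 11 |
| 10 | 50 | 5 | 500 + 50 + 250 = 800 | 40 |
| 20 | 50 | 5 | 1,000 + 100 + 250 = 1,350 | about 68 |

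The between-arm Z-tests form a further family of up to the same size. Correlation among features leaves these expected counts unchanged and makes the actual count more variable.

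**Does the r scale filter?** The smallest |r| with two-sided p < 0.05 is t/√(n − 2 + t²), where t is the 97.5% point on n − 2 degrees of freedom. This gives 0.31 at n = 40, 0.35 at n = 32, and 0.22 if all 80 patients are pooled. In a single-arm analysis every chance result therefore exceeds 0.30 and counts as at least moderate. In a pooled analysis it need not.

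**Share of significant results that are chance.** Let π be the fraction of pairs truly related. The share is 0.05(1 − π) / [0.05(1 − π) + power × π]. Power uses Fisher's z with variance 1.06/(n − 3). At n = 40 the standard error is √(1.06/37) = 0.169, so power is 45% for a true r of 0.30 and 90% for 0.50.

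| π | true r = 0.30 | true r = 0.50 |
|---|---|---|
| 1% | 92% | 85% |
| 5% | 68% | 51% |
| 10% | 50% | 33% |
| 20% | 31% | 18% |

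Chance results are the majority when π < 0.05/(0.05 + power): below 10% for r = 0.30 and 5% for r = 0.50. At n = 32 the limits are 12% and 6%; with 80 pooled they are about 6% and 5%.

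**Between-arm Z-test, n = 40 per arm.** The standard error is √(2 × 1.06/37) = 0.239. Power is 25% for 0.30 against 0 and 63% for 0.50 against 0. Chance is the majority below about 17% and 7% true differences.

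**Effect of false-discovery control.** In 300 simulated data sets with no relations, independent features and n = 40, the uncorrected rule gave on average 11.5 false results for 225 tests and 67 for 1,350. Benjamini-Hochberg at 5% gave about 0.06 in both, with any false result in 5-6% of runs.

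**The case against.** The strongest reply is that this is an openly declared exploratory screen. The network does not touch the primary outcome, the third objective is only to investigate interactions, and several places in the article use cautious language. An uncorrected screen labelled as hypothesis-generating is defensible. That stands, and it limits the seriousness of the point. It does not cover the Discussion's closing sentence, which claims more than a screen can give.

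The dimensions are also unknown. A reader might infer that every taxon is correlated with every miRNA and symptom, giving many thousands of tests. The documents do not say so: the miRNAs are narrowed in stages and the taxa are described as specific, although the same section also refers to the whole stool community. The smallest scenario above yields only about 5 chance results.

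The threshold sentence follows the Z-test directly and may govern only that test. The article also does not say whether networks are built by arm or pooled. Under the narrow reading the Z-tests are still uncorrected, and the edges have no significance rule at all.

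A reader might further infer that the Z-test is invalid because Fisher's usual standard error belongs to Pearson coefficients. The article does not state which variance will be used. Even with the usual one, simulated type I error was 5.0-5.4% at correlations of 0 to 0.3 and 5.9-6.6% at 0.5 to 0.7. This is a refinement, not a defect of the plan.

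**Conclusion.** The point holds in a limited form and should be fixed, though it does not threaten the trial's primary comparison. A stated uncorrected threshold, applied to an unspecified and probably large set of tests with all adjacent edges drawn, cannot carry a claim of demonstrated mechanism. The article contradicts itself on how strong this evidence will be, and the analysis supports only the weaker, exploratory version.

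The size rests on assumed feature counts: about 11 chance results among 225 tests, or about 40 among 800, if nothing is related. A reader might infer that most drawn edges will be chance, or that the third objective cannot be answered. Neither follows. Chance results are the majority only if true relations are scarce, below roughly 5-10% of pairs at 40 per arm; with 20% true pairs the chance share is 18-31%. The plan's rule gives no means of knowing which case applies.

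**What to change.** - In Tripartite Network Analysis, replace the uncorrected threshold with Benjamini-Hochberg false-discovery control, for example q < 0.05, over the tested correlations and over the between-arm difference tests. State that both sets are covered.
- Report the number of tests in each set.
- Show edges that pass only the uncorrected threshold as descriptive and hypothesis-generating, visibly distinct from those that survive.
- Reword the closing sentence of the Discussion so that efficacy *is associated with* the crosstalk, in line with the Abstract and Introduction.
- Optionally, test the between-arm differences by permuting arm labels.

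The cost is a few sentences and little computation, with no change to trial conduct. The real price is power: for r = 0.30 at n = 40 it is already only 45% uncorrected, so some weak true correlations will be lost. Benjamini-Hochberg is milder than Bonferroni, which for 500 tests would raise the required |r| from 0.31 to about 0.58. The choice should be fixed before the network is seen.

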## Methods

### Objectives

This trial aims to (1) re-evaluate the pure therapeutic effect of acupuncture for SCC; (2) identify the correlation between the gut microbiota and fecal miRNAs in patients with SCC; and (3) investigate the interactions among acupuncture-induced improvement of constipation symptoms, changes of fecal miRNAs and regulation of intestinal microbiota.

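### The network's direct and indirect effect labels follow from node type alone, so they carry no evidence on whether a taxon lies on the path to symptoms or is a bystander

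*Protocol article*

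**What the plan says.** All the rules at issue stand in the Tripartite Network Analysis section of the protocol article.

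- **Association measure.** The relations among efficacy, miRNAs and microbiome "will be investigated by computing Spearman's correlations in Matlab (version R2015b"). The threshold is "Significance will be considered at uncorrected *p* < 0.05".
- **Labels.** Results are reported as "direct (correlations with fecal microbiome) and indirect effects (clinical symptoms and differentially expressed miRNAs"), "with an emphasis on the association between microbiome and clinical efficacy".
- **Display.** "The networks will be presented based on selecting the gut microbiota counts and their first neighbors as nodes and all adjacent edges".

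The section's other tests are a Fisher r-to-z comparison of correlations between arms, analysis of variance and t-tests. None of them bears on direct versus indirect links. No partial correlation, mediation model or time ordering is stated.

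The network serves the third aim under Objectives, to "investigate the interactions among acupuncture-induced improvement of constipation symptoms, changes of fecal miRNAs and regulation of intestinal microbiota". The Discussion sets out several routes: miRNAs acting on colonic smooth muscle through SCN5A, miRNAs acting on gut bacteria and so on motility, and bacterial metabolites feeding back on miRNAs. Its closing sentence expects the results to establish that acupuncture works by modulating the miRNA–microbiota crosstalk.

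**The concern.** In the usual sense, a direct association is one that remains when the third variable is held fixed, and an indirect one runs through that variable. A pairwise correlation cannot tell the two apart. Here the words are assigned in advance: every correlation with a taxon is direct, and the symptom and miRNA layers are indirect. No result could make a microbiome correlation indirect or a miRNA–symptom correlation direct.

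The display rule adds to this. A miRNA correlated with symptoms but with no taxon is not a first neighbour of the microbiota through its own edges. Its link to symptoms may therefore be missing from the figure, although that is the pattern the SCN5A route would produce.

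What is at stake is the reading of the third objective. A figure headed with direct effects of the microbiome, followed by the Discussion's conclusion, invites a mechanistic claim that the analysis cannot support.

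**Working it through.** **1. The section's own figures.** The effect-size scale includes "0.30 moderate (9% variance explained), and 0.50 large (25% variance explained"). Variance explained is r²: 0.10² = 0.01, 0.30² = 0.09, 0.50² = 0.25. These reproduce exactly and are not in dispute.

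**2. The label rule.** Its only input is node type. Whatever the sign, size or conditional behaviour of a correlation, the label is the same. This step needs no assumption.

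**3. What a pairwise edge shows under different mechanisms.** Let M be a miRNA, B a taxon and S a symptom score, each path of strength r on a standard normal scale. The implied taxon–symptom correlation is:

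- M→B→S (taxon on the path): r
- M→S→B (taxon follows symptoms): r
- B→M→S (miRNA transmits the effect): r × r = r²
- M→B and M→S (taxon a bystander): r × r = r²

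Simulated share of trials with a significant B–S edge, labelled direct, at r = 0.6 (assumed; 4,000 runs; two-sided p < 0.05, sidedness assumed):

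| Mechanism | n = 32 | n = 40 | n = 80 |
|---|---|---|---|
| M→B→S | 94% | 98% | 100% |
| M→S→B | 94% | 98% | 100% |
| B→M→S | 49% | 60% | 88% |
| Bystander | 48% | 59% | 88% |

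The sizes come from Calculation of Sample Size: 40 is one arm, 80 is both arms, and 32 is one arm after the stated 20% drop-out (40 × 0.8).

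**4. Size of the bystander problem across r.** The critical |r| is 0.312 at n = 40 and 0.220 at n = 80. The true direct effect of the taxon is zero throughout.

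| r (assumed) | implied B–S correlation r² | shown as direct, n = 40 | shown as direct, n = 80 |
|---|---|---|---|
| 0.3 | 0.09 | about 8% | about 12% |
| 0.5 | 0.25 | about 32% | about 56% |
| 0.6 | 0.36 | about 58% | about 88% |

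Repeated runs agree to within about two percentage points. On the plan's own scale r = 0.3 is moderate and r = 0.5 large, so the larger rates need large links.

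**5. The display rule.** Take a true M–S link of 0.6, microbes unrelated to either, and n = 40. With 5 taxa, a significant M–S edge stays in the figure in 8% of runs if both its nodes must be neighbours of a taxon, and in 37% if one suffices. With 50 taxa it stays in 86% to 99%, but only because chance microbe edges bring its nodes in. The numbers of taxa are assumptions.

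**6. What conditioning can and cannot add.** The partial correlation is

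r(BS·M) = [r(BS) − r(BM) × r(MS)] / √{[1 − r(BM)²] × [1 − r(MS)²]}.

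- Bystander: the numerator is r² − r × r = 0. Simulated rejection is about 5–6%.
- M→B→S: at r = 0.6 the numerator is 0.6 − 0.6 × 0.36 = 0.384, the denominator √(0.64 × 0.8704) = 0.746, and the partial 0.51.
- M→S→B: r(BM) and r(MS) change places, so the partial is again 0.51. At n = 40 it is significant in about 90% of runs, as against 89% for M→B→S.

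Conditioning therefore separates a bystander from the other cases, but not cause from consequence. It has two further limits. With a true direct link at n = 40, power is about 39% at r = 0.3 and 78% at r = 0.5. If the miRNA is measured with reliability 0.5 (assumed), the 5–6% error at n = 40 rises to roughly 13–15% at r = 0.5 and 25–27% at r = 0.6.

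**The case against.** The best defence is that this is a display convention in an exploratory study. The disputed sentences concern how the network is drawn. The word direct follows straight after first neighbours and can be read in graph terms, as edges touching the focal nodes. The parenthesis openly defines it as correlations, and no test or decision depends on the label. Correlations among all three layers are computed before anything is drawn, and miRNA–symptom edges between retained nodes may still appear. The section MicroRNAs High-Throughput Sequencing Analysis also compares miRNAs between arms outside the network, so a miRNA without a linked taxon is not lost to the trial.

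Much of this stands. A reader might infer that the network presents the microbiome as the driver of improvement whatever the data say. The documents do not support that: the text never speaks of a driver, the correlations are undirected, and the presence, sign and strength of edges, and their differences between arms, all depend on the data. The display rule limits the figure and not the computation.

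The defence does not rescue the labels. The plan calls them effects, and the Discussion expects a causal conclusion, so a reader will not take the words as graph terms only.

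**Conclusion.** The point holds in a limited form. The direct and indirect labels are fixed by node type and carry no evidence on mechanism; this follows from the text without any assumption. The display rule can also keep from view a miRNA–symptom link that has no microbial neighbour.

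The size depends on an assumed single triple with equal link strengths. A bystander taxon is shown as a direct effect in about 8% to 58% of trials at n = 40, and 12% to 88% at n = 80, as r goes from 0.3 to 0.6. At moderate links this is little above the nominal 5%; at large links it is common.

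A reader might also infer that partial correlations would sort the edges correctly. They would not, because a taxon that merely follows symptoms passes the same test as one on the path, and many true links would fail it at these sample sizes. The matter concerns the third objective and not the primary outcome. It warrants a change because the change costs almost nothing and alters what the trial may conclude about mechanism.

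**What to change.** 1. In Tripartite Network Analysis, replace the terms direct and indirect effects with *microbiome correlations* and *miRNA–symptom correlations*.
2. Include in the network those significant miRNA–symptom edges that have no microbial neighbour.
3. Report, as supplementary exploratory estimates with confidence intervals, the partial Spearman correlations of symptom with taxon given the linked miRNA, and of symptom with miRNA given the linked taxon, both adjusted for arm. Do not classify an edge as direct or indirect by whether its partial correlation is significant.
4. In the closing sentence of the Discussion, state the expected result as an association between efficacy and the miRNA–microbiota crosstalk, and not as a demonstration that efficacy is achieved through it.

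The cost is a few sentences and a few lines of code on data already to be collected. The partial estimates are somewhat less precise than the pairwise ones: at n = 40 and r = 0.5, power for a true direct link is about 78% against 88%. The main price is that the network will support a weaker mechanistic statement.

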## Discussion

The onset of SCC is relatively complex and considered to be a result of abnormal intestinal function associated with multiple factors, such as the environment, psychology, diet, and life (1). Besides, the complexity of the pathogenesis can also be interpreted by the interactions between various pathetical mechanisms, including the changes in intestinal microbial community, weakened intestinal motility, the incidence of low-grade inflamed intestinal mucosa, and abnormal brain-intestine interactions (1, 32). With the occurrence of SCC, the quality of life and the psychological status of patients will be severely affected.

In the gene regulatory network, miRNA plays a central role different from the secondary intermediary role in the traditional central dogma, with the ability to accurately transmit and amplify signals. It has been proven that one miRNA harbors multiple target genes, and multiple miRNAs can cooperatively regulate the same target gene. In that way, there exist a series of complex regulatory networks, which are closely related to the onset and progress of various diseases with the involvement of multiple processes, such as cell proliferation, differentiation, apoptosis, and metabolism. According to the latest research, miRNAs are important targets in the research of functional constipation, owing to their functions in regulating the morphology and function of gastrointestinal motility-related cells (24–27). MiRNAs, such as miR-let-7f, miR-let-7e, and miR-200a-3p, were reported to be capable of decreasing the current density of NaV1.5 channel in colonic smooth muscle cells and thus increasing the contractile frequency and amplitude of smooth muscle strips via inhibiting the expression of target gene SCN5A (24). In an animal experiment, miR-128 was found to present significantly elevated expression in the colonic tissue of mice with functional constipation, which inhibited the p38α/M-CSF signaling pathway leading to impaired function of Cajal cells (33). The imbalance of intestinal microbiota caused by the disorders of miRNA and related regulatory networks is important for the pathogenesis of SCC. It is known that miRNAs which are differentially expressed can target a variety of intestinal bacteria, resulting in colonic motor disorder and secretion reduction (34, 35). In the meantime, the bacterial metabolites exert a negative feedback function on miRNAs, making the symptoms of constipation protracted (36).

Electroacupuncture can improve gastrointestinal peristalsis, promote the contraction of distal colon, and accelerate the whole intestinal transport in both healthy and constipated conditions (4). Acupuncture can not only regenerate damaged intestinal neurons and regulate the activities of intestinal nervous system, but also makes effects on serum motilin, ghrelin, gastrin, and bile acid (11). Based on our previous research, intestinal microbiota was identified to play an important role in the improvement of intestinal motility by acupuncture therapy in SCC patients (21). Therefore, the objective of this study is to preliminarily reveal the effector mechanism by which acupuncture regulates miRNAs and gut microbiota.

There are also certain limitations should be noted. First, it is remarkably hard to differentiate IBS-C from SCC using the ROME IV criteria, which makes the differential diagnosis more difficult. Second, the relatively small number of samples and the inability to strictly control the daily diets of participants, which may impact the findings. Third, owing to the short follow-up period, the potential value of miRNAs and gut microbiota in the long-term efficacy of acupuncture will remain unknown. In conclusion, the results of this trial are expected to not only provide clinical evidence of the efficacy of acupuncture in treating SCC, but demonstrate that this efficacy is achieved by modulating the crosstalk between fecal miRNAs and gut microbiota.

